## Abstract

**Background:**

This paper describes the protocol for the Nano X Image Guidance (Nano X IG) trial, a single-institution, clinical imaging study. The Nano X is a prototype fixed-beam radiotherapy system developed to investigate the feasibility of a low-cost, compact radiotherapy system to increase global access to radiation therapy. This study aims to assess the feasibility of volumetric image guidance with cone beam computed tomography (CBCT) acquired during horizontal patient rotation on the Nano X radiotherapy system.

**Methods:**

In the Nano X IG study, we will determine whether radiotherapy image guidance can be performed with the Nano X radiotherapy system where the patient is horizontally rotated while scan projections are acquired. We will acquire both conventional CBCT scans and Nano X CBCT scans for 30 patients aged 18 and above and receiving radiotherapy for head/neck or upper abdomen cancers. For each patient, a panel of experts will assess the image quality of Nano X CBCT scans against conventional CBCT scans. Each patient will receive two Nano X CBCT scans to determine the image quality reproducibility, the extent and reproducibility of patient motion and assess patient tolerance.

**Discussion:**

Fixed-beam radiotherapy systems have the potential to help ease the current shortfall and increase global access to radiotherapy treatment. Advances in image guidance could facilitate fixed-beam radiotherapy using horizontal patient rotation. The efficacy of this radiotherapy approach is dependent on our ability to image and adapt to motion due to rotation and for patients to tolerate rotation during treatment.

**Trial registration:**

ClinicalTrials.gov, NCT04488224. Registered on 27 July 2020.

## Background

Radiotherapy plays a crucial role in the treatment of cancer patients, with just under half indicated to benefit from its inclusion in their treatment regime [1]. Cancer incidence is predicted to grow from 18.1 million cases reported in 2018 to 29.4 million by 2040. This increased incidence translates to greater demand for radiotherapy for which there is already a global shortfall, particularly in low- and middle-income countries [2]. Substantial investment is required to grow the global number of megavoltage radiotherapy units from around 14,000 to the estimated 21,800 required to meet demand by the year 2035 [3]. Furthermore, global geographic disparities in cancer outcomes exist, such as the correlation between radiotherapy machine availability and the gross income per capita as well as poorer cancer-reported outcomes in low- and middle-income countries. In order to meet growing demand and increase global access to radiotherapy, particularly for low- and middle-income countries and for rural areas in high-income countries, compact and low-cost radiotherapy solutions may be necessary.

Fixed beam radiotherapy systems, where the primary treatment beam is kept stationary and the target is moved and rotated, are extensively used in particle beam therapy to reduce the size and cost of the systems. The same concept could be applied to conventional X-ray linear accelerators to assist with meeting global radiotherapy demand. A small, economic ‘Nano X’ linear accelerator has been designed, prototyped and investigated based on this concept (Fig. 1) [4–8]. The Nano X has a novel design that relies on software to compensate for patient motion during imaging and treatment. Unlike conventional radiotherapy system where the heavy gantry is rotated, the Nano X design applies the inverse approach to conventional radiotherapy systems by using horizontal patient rotation and a fixed, vertical treatment beam. As the patient is expected to move during horizontal rotation, X-ray imaging is utilized to verify the patient position before and during treatment and adapt the radiation beam if necessary. This design provides simplification to the linac and a reduction in the bunker size and shielding requirements.

**Fig. 1 Fig1:**
[figure not shown]
The components (left) and geometric configuration (right) of the prototype Nano X linear accelerator

The Nano X radiotherapy system faces two primary challenges: (1) imaging and treatment delivery in the presence of anatomical deformation due to patient rotation and (2) patient acceptance and tolerance of rotation. This study aims to evaluate the feasibility of volumetric imaging for treatment guidance using cone beam CT (CBCT) on the Nano X fixed-beam radiotherapy system. In this case, the patient is rotated around the horizontal axis, and the kV imaging system is held stationary. The feasibility of the Nano X CBCT imaging will be evaluated by comparing the image quality of the Nano X CBCT reconstructions to conventional CBCT reconstructions. Furthermore, we aim to quantify the patient response to horizontal rotation.

## Methods

Volumetric patient imaging with CBCT requires the X-ray projections to be acquired from a wide range of angles. This is achieved in conventional radiotherapy systems by rotating an X-ray source around the patient. The feasibility of CBCT imaging on the Nano X radiotherapy system, where the X-ray source is stationary and the patient is rotated horizontally, will be assessed in this single-institution, clinical imaging study. This study will recruit 30 radiotherapy patients at Nelune Comprehensive Cancer Centre (NCCC) at Prince of Wales Hospital (POWH). In addition to a conventional CBCT, patients will receive a CBCT scan while undergoing horizontal rotation on the prototype Nano X radiotherapy system. Patient images acquired with these two methods will be assessed for image quality by a group of qualified observers. The study schema is shown in Fig. 2.

**Fig. 2 Fig2:**
[figure not shown]
The study schema for the Nano X Image Guidance study. The CLQ, STAI and FMS questionnaires ask about claustrophobia, anxiety and motion sickness, respectively

The prototype Nano X consists of an Elekta Synergy linac at a fixed gantry angle of 0° and a bespoke patient rotation system (PRS). The Nano X prototype has been developed and extensively tested against 161 design, safety and usability specifications in accordance with the appropriate standards pertaining to the performance and safety of medical electrical equipment and medical linear accelerators [6]. The system was commissioned as reported by Liu et al. [8].

### Study design

This study is a single-arm blinded comparison study. The study involves up to three additional CBCT scans to be acquired for each patient, two of which will be performed on the Nano X radiotherapy system with the participant horizontally rotated and the kV imaging system held stationary (Nano X CBCT scan). Nano X CBCT scans will be used for study purposes only; patients will be treated on a conventional radiotherapy system. Study participants will be asked to attend an imaging session following two of their standard-of-care radiotherapy treatment fractions. During each of two study visits the participant will receive one Nano X CBCT scan.For participants who receive a conventional CBCT scan for image guidance during their standard-of-care radiation therapy treatment, this imaging data will be collected for study analysis and image quality comparator. These participants will receive a total of two CBCT scans (Nano X CBCT scans) in addition to standard treatment procedures over the course of the study.For participants who do not receive a conventional CBCT scan for image guidance during their standard-of-care treatment delivery (e.g. for breast cancer treatment where MV imaging is often employed), one additional conventional CBCT scan will be performed during their treatment fraction on the same day as one of the Nano X CBCT scans. These participants will receive a total of three CBCT scans in addition to standard treatment procedures (1 conventional and 2 Nano X CBCT scans).

The projections from the Nano X CBCT scan will be reconstructed offline following the participant visits.

The feasibility of using Nano X CBCT scans for volumetric image guidance will be assessed by comparing the image quality to a conventional CBCT scan of the same participant from their routine treatment (see the ‘Primary endpoint and assessment’ section).

The claustrophobia questionnaire will be administered only once before the first study session. Prior to each Nano X CBCT scan, patients will complete the anxiety and motion sickness questionnaires. Patients will then be immobilised on the Nano X PRS using safety strapping and computerised airbag restraints. The patient will undergo one continuous horizontal rotation that will take up to 3 min to complete. A Nano X CBCT scan will be acquired during the rotation. Following the scan, patients will again complete the anxiety and motion sickness questionnaires. Patients will undergo a semi-structured interview after their second session to assess their experience.

Data collected from the patients’ standard of care radiation therapy include patient demographics, treatment planning CT/4DCT, orthogonal planar kV images/CBCT/4DCBCT scans, treatment plans and structure set containing contours.

### Sample size

This study is a pilot feasibility study, and prior data is unavailable for sample size estimation. Therefore, a sample size of 30 was determined based on the feasibility of participant recruitment, the necessities of examining feasibility [9] and diminishing returns in precision for sample sizes exceeding this value [10].

### Key selection criteria

#### Inclusion

Cancer patients, aged 18 years or older, who are receiving radiation therapy and are able to be imaged using the Nano X PRS, with one of the following tumour sites: (a) in the head/neck region, (b) in the chest/abdomen region with fast CBCT used for standard of care image guidance and aged 60 years or older, (c) in the chest/abdomen region not receiving CBCT for standard of care image guidance and aged 70 years or older or (d) diagnosis of lung cancer with stage II-IV. ECOG Performance Status 0–2. The ability to communicate fluently in English to facilitate safe on- and off-boarding of the PRS and communication of comfort or distress to operators of the equipment throughout the session.

#### Exclusion

Patient positioning limitations of the Nano X PRS mean that tumour targets outside of the head/neck region and as far down as the abdomen cannot be imaged are not included. Patients outside the age restrictions stated above are excluded to due to legislated dose limits [11]. Patients with severe vertigo or with a recent diagnosis of benign paroxysmal positioning vertigo, weight > 137 kg (weight restriction of couch), pregnant women and patients from whom attaining informed consent would not be possible, including mental impairment, are also excluded.

### Primary endpoint and assessment

The primary objective of this pilot stage study is to determine whether CBCT volumetric image guidance is feasible for radiotherapy on a fixed-beam radiotherapy system using horizontal patient rotation. Feasibility will be assessed by comparing the image quality of reconstructed Nano X CBCT scans against conventional CBCT scans.

To measure the success of this objective, a combination of both objective and subjective image quality metrics will be used. For the subjective image quality metric, a group of experienced observers will perform image quality evaluations on a patient’s conventional CBCT scan and a Nano X CBCT scan side-by-side with 3 orthogonal views while blinded to the acquisition method. The image quality will be graded considering geometric accuracy, anatomical visualisation, sharpness of the image, soft tissue contrast, image noise and uniformity and overall clinical usability. Observers will be asked to indicate whether the image sets are of sufficient quality for image guidance, to select which CBCT scan set they deem to have superior image quality and whether it is of comparable, slightly superior or far superior image quality to the second CBCT scan. Observer responses will be assigned a score on a 5-point scale according to the study of Gardner et al. [12]. This metric is a subjective measurement of image quality; however, unlike quantitative image quality metrics, the observer scores provide a clinically relevant assessment of image quality and are robust to changes in patient anatomy between CBCT scans.

For the objective image quality metrics, a combination of standard metrics will be used, including signal-to-noise ratio (SNR), contrast-to-noise ratio (CNR) and edge-response width (ERW). These metrics evaluate both the spatial accuracy of the reconstructed CBCT images, as well as the reconstruction quality. The combination of both the objective and subjective image quality metrics provide a robust method for evaluating the image quality in a way that is robust and clinically relevant.

### Statistical analysis

Volumetric image guidance will be considered feasible for Nano X CBCT scans if the majority of reconstructed Nano X CBCT scans are either (1) deemed to have equivalent image quality to a corresponding conventional CBCT (image quality scores ≤ 3) or (2) the image quality is deemed sufficient for image-guided radiotherapy by a group of experienced observers. In this case, the majority is defined as a pass rate including uncertainty interval (one standard deviation) greater than 66% (e.g. 21 of the 30 participants Nano X CBCT scans pass).

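### The feasibility rule counts reconstructed scans while its example counts 30 participants, so a participant without a usable scan can leave the denominator, and which of two scans is scored is not fixed

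*Protocol article*

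**What the plan says.** In the Statistical analysis section that follows Primary endpoint and assessment, volumetric guidance is called feasible if "the majority of reconstructed Nano X CBCT scans" pass by either of two routes: an image quality score of 3 or less against the conventional scan, or a judgement by the observers that quality is sufficient for guidance. Majority is defined as "a pass rate including uncertainty interval (one standard deviation) greater than 66" per cent, and the illustration is "e.g. 21 of the 30 participants Nano X CBCT scans pass".

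The Study design section states: "During each of two study visits the participant will receive one Nano X CBCT scan". With 30 participants that is up to 60 scans. It adds that projections are reconstructed offline after the visits, so an attempted scan and a reconstructed scan are different things.

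Primary endpoint and assessment has observers compare "a patient’s conventional CBCT scan and a Nano X CBCT scan side-by-side with 3 orthogonal views": one Nano X scan per patient, not identified as the first or the second. The Abstract and the secondary endpoints section give the repeat scan to reproducibility, motion and tolerance.

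The Sample size section says that "a sample size of 30 was determined based on the feasibility of participant recruitment" and that no prior data exist. No rate of failed or missing scans is given.

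**The concern.** The go/no-go criterion carries two units, and they agree only if every participant yields exactly one scored reconstruction. Both pass routes need an image to look at, so a scan that was never acquired, was stopped, or could not be reconstructed has no result under either. Under the literal wording it is not counted. Under the example, with 30 as the base, it is not among the passes and so works as a fail.

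The difference matters because the Background names imaging under rotation-induced deformation and patient tolerance of rotation as the system's two main challenges. A participant from whom no image can be produced is informative about feasibility. Removing that participant lowers the number of successes needed, in a rule that a few participants decide. An index scan that is not named leaves a second route by which the pass rate could rise.

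**Working it through.** **Inputs.** From the article: 30 participants, two Nano X scans each, threshold 66%, a one-standard-deviation interval, example 21 of 30. Assumed, because the article gives no figures: 0 to 10 participants without a usable scan; a single-scan pass probability p of 0.50 or 0.60; a within-patient correlation ρ from 0 to 1. The standard deviation is taken as binomial, SD = √(r(1−r)/n), where r is the observed rate.

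**The plan's own figure.** 21/30 = 70.0%; SD = √(0.70 × 0.30/30) = 8.4 points; interval 61.6% to 78.4%. The smallest passing count of 30 is:
- 20 if the point estimate must exceed 66% (20/30 = 66.7%);
- 21 if it must strictly exceed two-thirds and the SD is ignored;
- 23 if the rate minus one SD must exceed 66% (23/30: 76.7 − 7.7 = 68.9%; 22/30: 73.3 − 8.1 = 65.3%);
- 18 if the rate plus one SD must exceed 66%.

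Only the second gives 21. How the SD enters is a separate question, so the denominator is checked below on both the point-estimate and the minus-one-SD readings.

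**Step 1: denominator.** With m participants without a usable scan, n = 30 − m. The table gives the smallest passing count, with that count as a share of all 30 in brackets.

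| m | n | point estimate > 66% | rate − SD > 66% |
|---|---|---|---|
| 0 | 30 | 20 (66.7%) | 23 (76.7%) |
| 1 | 29 | 20 (66.7%) | 22 (73.3%) |
| 2 | 28 | 19 (63.3%) | 21 (70.0%) |
| 4 | 26 | 18 (60.0%) | 20 (66.7%) |
| 5 | 25 | 17 (56.7%) | 19 (63.3%) |
| 10 | 20 | 14 (46.7%) | 16 (53.3%) |

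The same successes can therefore give opposite conclusions:
- Point estimate, 17 passes and 5 unusable: 17/25 = 68.0% passes; 17/30 = 56.7% fails.
- Rate minus SD, 20 passes and 4 unusable: 20/26 = 76.9%, less 8.3 = 68.7%, passes; 20/30 = 66.7%, less 8.6 = 58.1%, fails. On the point-estimate reading both of these pass, so this contrast belongs to the stricter reading only.

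**Step 2: which scan is scored.** If either scan could count, P(at least one passes) = p + (1 − ρ)p(1 − p). For p = 0.50 and ρ = 0.5 this is 0.50 + 0.5 × 0.25 = 0.625. The binomial chance of meeting the bar in 30 participants is then:

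| p, bar | one named scan (same as ρ = 1) | ρ = 0.8 | ρ = 0.5 | ρ = 0 |
|---|---|---|---|---|
| 0.50, ≥ 21 | 2.1% | 6.9% | 25.8% | 80.3% |
| 0.60, ≥ 23 | 4.4% | 11.9% | 36.8% | about 91% |

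At ρ = 1 there is no inflation. ρ = 0 is an extreme, since two scans of one patient will tend to agree.

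**The case against.** The strongest reply is that the example settles the matter: 21 of 30 uses the whole planned sample with one result each, which points to a per-participant denominator. This stands in part. It means that removal of failed participants is one reading of the rule and not an established fact. It does not remove the conflict, because the operative wording still conditions on reconstruction.

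Second, primary feasibility is defined as image quality, and the Discussion assigns tolerance chiefly to another study. Counting an intolerant participant as a primary failure is therefore a design choice. That is fair. An unreconstructable scan, however, is a failure of imaging and falls within the primary question.

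Third, an article may leave missing-scan handling and the index scan to the full protocol or analysis plan. That would answer a mere omission, but not two units inside one stated rule.

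Several stronger readings are tempting and are not supported:
- *The better of two scans will be used.* Nothing says so; it is only not ruled out.
- *All 60 scans will be pooled as independent.* The observers score one Nano X scan per patient, the example counts participants, and the repeat scan is assigned to reproducibility.
- *Participants who move too much drop out.* Motion is expected, and motion-compensated reconstruction is an objective. Motion normally yields a degraded image, which is scored and can fail.
- *The choice of conventional scan biases the result.* No direction or size can be shown, and the sufficiency route needs no comparator.
- *Early stoppers are lost from the tolerance data.* The article says "Patients will undergo a semi-structured interview after their second session to assess their experience" and is silent on those who stop sooner. That bears on a secondary objective, not on this rule.

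**Conclusion.** The point holds as an inconsistency in a stated decision rule that can produce a wrong feasibility conclusion. The rule and its example use different units, the handling of a participant without a usable scan follows from neither with certainty, and the scored scan is not identified. Any resulting error runs in favour of declaring feasibility.

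Its size depends on an unknown number of unusable participants. With none, the denominator has no effect. With one, the point-estimate bar stays at 20. With 5, the bar drops by 3 passes on the point-estimate reading and 4 on the minus-one-SD reading; with 10, by 6 and 7. The effect of scan choice is conditional: it arises only if the choice is made after reconstruction, and it ranges from nothing at correlation 1 to large at low correlation. The article supports saying that these routes are open, not that they will be used. This should be corrected, but it does not undermine the design.

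**What to change.** Reword the primary rule so that one unit runs through it:
- Define the pass rate per participant. The denominator is every participant positioned for the session 1 rotation.
- Count a session 1 scan that is not acquired, is stopped or cannot be reconstructed as a fail.
- Name the session 1 scan as the index scan in advance, and use the second scan for reproducibility only, in line with the role the article gives it.
- Report the pass rate among reconstructed scans as a supporting figure, with the number of unusable scans and the reasons. Readers can then separate image quality from failure to obtain an image.

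The change is to wording and counting. It uses scans already planned and leaves the timing of the conventional scans as it is. The downside is that the pass rate can be lower, because failures count. It should be settled before the observers read any scan.

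### The 21-of-30 example of the feasibility rule fails that rule on its natural reading, which needs at least 23 of 30

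*Protocol article*

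**What the plan says.** The rule is in the Protocol article, in the Statistical analysis section that follows Primary endpoint and assessment. A scan can pass in two ways: it is "deemed to have equivalent image quality to a corresponding conventional CBCT (image quality scores ≤ 3"), or the observers find it good enough for image-guided radiotherapy. Feasibility then requires a majority of passes, defined as a "pass rate including uncertainty interval (one standard deviation) greater than 66% (e.g. 21 of the 30 participants Nano X CBCT scans pass"). Rule and example stand in the same sentence.

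Under Sample size, "a sample size of 30 was determined based on the feasibility of participant recruitment" among other practical grounds, and the text adds that "prior data is unavailable for sample size estimation". The article states no alpha, power or target pass rate. This sentence is the only numerical criterion for the primary objective.

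**The concern.** A margin of one standard deviation is normally there to make a threshold harder to reach: the rate must still exceed 66% after allowing for sampling error. With 30 participants, one binomial standard deviation is about 8 points, and the example rate of 70% is only 4 points above the threshold. The example therefore seems to breach the rule that it illustrates.

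The primary conclusion is at stake. If 21 or 22 participants' scans pass, an analyst who follows the example reports feasibility, and one who applies the rule in its natural sense does not. The text does not say which is right, so the choice could be made after the data are seen.

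**Working it through.** **Inputs.** n = 30 (Sample size). Threshold 66%, margin of one standard deviation and example of 21/30 (Statistical analysis, primary endpoint). The article gives no formula for the standard deviation. I assume the binomial standard deviation of the observed pass rate, with participants as independent units.

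**Formula.** p = x/30; SD = sqrt(p(1 − p)/30); interval p ± SD.

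**The article's example.** p = 21/30 = 70.0%. SD = sqrt(0.70 × 0.30/30) = 8.4 points. The interval runs from 61.6% to 78.4% and contains 66%.

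**Neighbouring counts.**

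| Passes | Rate | SD (points) | Lower limit | Upper limit | Lower limit above 66%? |
|---|---|---|---|---|---|
| 18 | 60.0% | 8.9 | 51.1% | 68.9% | no |
| 20 | 66.7% | 8.6 | 58.1% | 75.3% | no |
| 21 | 70.0% | 8.4 | 61.6% | 78.4% | no |
| 22 | 73.3% | 8.1 | 65.3% | 81.4% | no |
| 23 | 76.7% | 7.7 | 68.9% | 84.4% | yes |

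**Other ways to form the lower limit.** At 21/30, a variance with n − 1 gives 61.5%, Wilson 61.1%, Jeffreys 61.1% and Clopper-Pearson 59.4% (the last two at one-SD coverage, 68.3%). With the SD taken at the threshold, sqrt(0.66 × 0.34/30) = 8.6 points, so the rate must exceed 74.6%; 30 × 0.746 = 22.4, which again means 23.

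**Readings on which 21/30 passes.**
- Standard deviation ignored: 70.0% > 66%. The smallest passing count is then 20 (66.7%), or 21 if 66% stands for strictly more than two-thirds.
- Upper limit used: 78.4% > 66%. The smallest passing count is then 18, because 17/30 has an upper limit of 65.7%.
- Some other standard deviation, for example between observers: 70 − 66 = 4, so it must be below 4 points. The article gives no such figure.

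**Effect on the conclusion.** Exact binomial probability of declaring feasibility, n = 30:

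| True pass rate | Cut-off 21 | Cut-off 23 | Difference = P(21 or 22 passes) |
|---|---|---|---|
| 60% | 18% | 4% | 13% |
| 66% | 40% | 15% | 25% |
| 70% | 59% | 28% | 31% |
| 80% | 94% | 76% | 18% |

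Differences were taken before rounding (at 60%: 17.6 − 4.4 = 13.2).

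**The case against.** The strongest reply is that the failure depends on two things the article does not state: that the standard deviation is binomial over participants, and that the lower limit is the one compared with 66%. That is correct. A reader might go further and infer that 21 cannot be the cut-off on any reading, or that the example simply overlooks the uncertainty clause. The article does not support either inference:

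- If 66% is a shortened two-thirds, strictly more than two-thirds of 30 means more than 20, so 21 is the minimum. This reading does leave the clause without a function.
- Several observers score the scans, so a between-observer standard deviation is conceivable. If it lay between about 0.7 and 4.0 points, 20/30 would fail (66.7 − 66 = 0.7) and 21/30 would pass. The clause would then be respected and 21 would be the minimum.

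Two further points are fair. The example is introduced with e.g., so 21 need not be the minimum; but an example must satisfy its own rule. The denominator is also open to question, because each participant has two Nano X scans (Study design). Over 60 scans, ignoring clustering, 44/60 has the same rate as 22/30 and would pass (lower limit 67.6%), while 42/60, the same rate as the example, would still fail (64.1%). The example itself counts participants.

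It can also be said that a formula may be left to an analysis plan, and that this is a pilot. The first excuses the missing formula, but not an example that disagrees with the rule on its natural reading. The second does not help much, because the article attaches a numerical declaration of feasibility to its primary objective.

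**Conclusion.** Wrong as written. With a binomial standard deviation over 30 participants and the lower limit required to exceed 66%, the article's example gives 61.6% and fails, and the smallest passing count is 23. The example can be rescued only by ignoring the standard deviation, by using the upper limit (which would also admit 18/30, a rate of 60%), or by supposing an unstated standard deviation below 4 points. Nothing else in the article settles which was meant.

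The practical gap is 21 against 23. One could stretch it to 28 by using the standard deviation of a single pass/fail observation, but that is not a plausible interval for a rate and I give it no weight. Within the realistic gap, results of 21 or 22 are ambiguous. If participants are independent, they occur with probability 25% at a true pass rate of 66% and 31% at 70%.

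**What to change.** Before the scores are analysed, make the rule and the example agree by stating what the standard deviation is taken over, which limit is compared with 66%, and the resulting minimum count. The article does not show which half of the sentence is the intended one, so the sponsor must choose:

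- **Keep the uncertainty clause.** For instance: feasible if the pass rate over participants minus sqrt(p(1 − p)/n) exceeds 66%, that is, at least 23 of 30.
- **Keep 21 of 30.** Delete the uncertainty clause, state the rule as a point estimate of more than two-thirds, and report that it passes about 40% of the time at a true rate of 66%.

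Either option costs one sentence and needs no additional participants or scans. The first makes the threshold slightly stricter than the printed example, lowering the chance of declaring feasibility at a true rate of 80% from 94% to 76%.
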